## **SUMMARY OF THE MOST IMPORTANT GOALS OF THE PROJECT**

**PROPOSAL:** Gestational diabetes mellitus (GDM) is a growing health problem associated with adverse pregnancy and birth outcomes. It is also considered an established risk factor for the development of type 2 diabetes and cardiovascular disease over longer term for both women and the offspring. Its incidence is increasing, not only as a result of the application of more stringent criteria of diagnosing. In the last years, there has been a dramatic increase in the prevalence of prepregnancy obesity, a main risk factor for maternal and neonatal morbidity and mortality, as a direct consequence of the global obesity epidemic. Recent data suggest that the prevalence of obesity in reproductive-age women is around 10% in Spanish women. The origin of this epidemic is an unhealthy lifestyle, with high-energy and high-fat containing diets, physical inactivity and smoking. Of interest, there is now substantial evidence for the importance of the intrauterine environment on the health and longevity of the offspring, although the mechanisms underlying remain poorly understood. The Mediterranean Diet (MedDiet) has been associated with greater longevity and quality of life, and with potential advantages in the prevention of cardiovascular diseases. Thus, in this project we will attempt to study the effect of a lifestyle intervention based on a MedDiet and physical activity/exercise performance, beginning after the 1st gestational visit [8-12 gestational weeks (GWs)] and throughout the pregnancy, in the incidence of GDM rate. In addition, we will investigate its impact on genetic and epigenetic (DNA methylation and microRNAs expression) pattern expression, and gut microbiome composition both in women and in the offspring. Since GDM evolves through loops of deregulated inflammation, genetic/epigenetic modifications, gut microbiota and diet, we believe that the synergic analysis of such parameters could provide new biological insights and effective biomarkers that could have applications in prevention, molecular diagnosis and prognosis of GDM. The idea of preventing, or even managing, diseases such as diabetes or obesity with diet is very attractive but deserves further studies.

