### **Secondary outcome:**

- To define functional genetic risk of developing GDM focusing in obese and non obese pregnant women.
- To investigate the effects of MedDiet and physical exercise/activity scheduled in inflammatory biomarkers in pregnant women.
- To investigate the effects of MedDiet and physical exercise/activity scheduled in the epigenetic mechanisms (DNA methylation and miRNA expression) in pregnant women and offspring; if so, it would represent a novel epigenetic mechanism for regulation of gene expression in the offspring.
- To investigate whether the MedDiet and physical exercise/activity scheduled alters the composition of the gut microbial flora both in women and offspring.
- To evaluate the impact of all these parameters on the long-term health of newborns in the first year of life.
- To estimate changes in HbA1c, insulin, HOMA, lipid profile, body weight, blood pressure, adherence to changes in lifestyle estimated by Med Score and urinary hydroxytyrosol levels and plasma  $\gamma$ -tocopherol levels to confirm compliance in the group receiving MedDiet [extra virgin olive oil (EVOO) and pistachios].
- The parameters to be assessed will be: gestation duration and fetal development; delivery characteristics such as caesarean delivery and instrumental vaginal birth, placental weight; and newborn data such as newborn weight, Apgar test values and cord blood pH.

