## **STATISTICAL ANALYSIS**

Analysis of all the variables pertaining to efficacy will be performed on an intention-to-treat basis, including data on all patients randomized and all available follow-up data.

The Student's t test or ANOVA [nonparametric test (RANK TEST)] will be used to compare continuous variables [and expressed as means standard deviation (SD)] while categorical variables will be compared using the chi-squared test. The association between qualitative variables will be analyzed by the chi-squared test or Fisher's exact test in case more than 25% of the expected values will be less than five. In the case of ordinal variables, the hypothesis of ordinal proportion tendency will be tested.

Relative risk will be assessed together with its 95% confidence interval, using Cornfield's method. In all cases, the distribution of the variable versus the theoretical models will be checked, and the variance homogeneity hypothesis will be tested. The paired Student's t test or a repeated measures analysis of variance (MANOVA) will be used to compare continuous variables. The changes in variables with time (pre- and post-treatment) will be estimated by a MANOVA. Variables included will be treatment and study period. Mathematical models will be chosen by the type of variable and used logistic analysis, linear regression or Cox regression. The existence of interactions will be evaluated. Variables showing a p value under 0.15 in the univariate analysis will be selected for the multivariate analyses. The null hypothesis will be rejected in each statistical test when  $p < 0.05$ . Analysis will be performed using windows SPSS version 17.0 software and STATA 12.

Interim analyses: No applicable.

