### Statistical analysis.

Variables are presented with their frequency distribution. Quantitative variables are summarized by their mean and standard deviation ( $\pm$ SD). All primary analyses were performed on an intention-to-treat basis. Comparison between baseline group characteristics and primary and secondary outcomes for qualitative variables were evaluated by the chi-squared test. For quantitative variables, measures were compared through Student's t test or the nonparametric Mann-Whitney U test if the quantitative variables would not adjust to a normal distribution. The Shapiro-Wilk test was used to verify the normal distribution of data.

Logistic regression analyses were used to assess the effect of the intervention for the primary and secondary outcomes that were significantly different in the univariate analysis. The magnitude of association was evaluated using the odds ratio (OR) and 95% confidence interval (CI). A crude and 5 multivariate models were fitted: model 1 was adjusted for age (continuous) ethnicity and parity; model 2 adjusted for pregestational BMI and gestational weight gain (continuous); model 3 adjusted for gestational, personal and family history, and smoker status (never, current, or former smoker); Model 4 adjusted for the variables in Models 1 and 2; and Model 5, adjusted for the variables in Models 1-3. These models 4 and 5 were only fitted for the primary outcome due to the small number of events in many of the secondary outcome variables.

All *p* values are 2-tailed at less than 0.050. Analyses were done using SPSS, version 21 (SPSS, Chicago, Illinois).

ADENDUM April 01, 2017.

Statistical analysis.

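### The protocol fixes an unadjusted p<0.05 for every test and makes no exception for the methylation, miRNA and gut microbiome outcomes

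*Protocol*

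**What the plan says.** The protocol's Statistical Analysis section gives a general rule: "The null hypothesis will be rejected in each statistical test when" p is below 0.05. The later Final statistical analysis section restates it, saying that all p "values are 2-tailed at less than 0.050". The April 2017 addendum changes how relative risks are estimated and leaves the threshold alone. None of these sections mentions multiplicity, a false discovery rate or an outcome family to which the threshold does not apply.

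The list of secondary outcomes includes "epigenetic mechanisms (DNA methylation and miRNA expression) in pregnant women and offspring", and whether the intervention "alters the composition of the gut microbial flora both in women and offspring". The project summary expects the combined molecular analysis to offer "effective biomarkers that could have applications in prevention, molecular diagnosis and prognosis of GDM". The same list also names metabolic, obstetric and neonatal measures. None of the secondary outcomes is labelled exploratory.

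**The concern.** A 5% threshold per test is sound for one prespecified primary comparison. Applied feature by feature to methylation sites, miRNAs or bacterial taxa, it returns nominally significant features in proportion to the number tested, even if the diet changes none of them. Such a list cannot be told apart from a real signal by its p values alone.

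What is at stake is the mechanistic half of the project, which features in the trial's title and is tied to the biomarker ambition. The conclusion on prevention of gestational diabetes is not at stake. The point also cannot be set aside as something that belongs in a separate analysis plan. The protocol has already fixed the rule, twice, and a plan that applied false discovery rate control would depart from the protocol's wording.

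**Working it through.** **Inputs.** The per-test level of 0.05, two-sided, comes from the Statistical Analysis and Final statistical analysis sections. The sample size inputs (35% control incidence, 30% relative reduction, 80% power, 315 per group) come from the Sample size subsection. The number of molecular features, m, is not in the protocol. It is an assumption here, shown from 1 to 10,000.

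**1. The plan's own figure.** A 30% relative reduction from 35% gives 0.35 × 0.70 = 24.5%. Two proportions of 35% and 24.5%, two-sided 0.05 and 80% power, need 316 per group with a continuity correction and 297 without. The stated 315 therefore agrees with the corrected formula, to within one woman. It uses the full 0.05 for a single primary outcome, so nothing below changes it.

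**2. False positives when m true nulls are each tested at 0.05.**

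- Expected number = 0.05 × m. This holds whatever the correlation between features.
- Chance of at least one = 1 − 0.95^m. This assumes independent features.

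| m (assumed) | Expected false positives | Chance of at least one |
|---|---|---|
| 1 | 0.05 | 5% |
| 5 | 0.25 | 22.6% |
| 10 | 0.5 | 40.1% |
| 20 | 1 | 64.2% |
| 50 | 2.5 | 92.3% |
| 100 | 5 | 99.4% |
| 1,000 | 50 | about 100% |
| 10,000 | 500 | about 100% |

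A short candidate panel and a broad screen are thus very different cases, and the protocol does not say which is meant. Positive correlation between features lowers the last column but not the middle one.

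**3. The clinical and laboratory secondary outcomes.** The last two bullets of the secondary outcome list, with the lipid profile and fetal development each counted once, give 17 measures. Three of them (the diet score, urinary hydroxytyrosol and plasma γ-tocopherol) measure adherence. The intervention should move these, so they are not plausible nulls. That leaves 14: six metabolic or physical (HbA1c, insulin, HOMA, lipids, weight, blood pressure) and eight obstetric or neonatal. If all 14 were independent nulls, the chance of at least one false positive would be 1 − 0.95^14 = 51%. Several are clearly related, such as insulin with HOMA, or gestation length with newborn weight, so 51% is best read as an upper guide.

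**4. What control would mean per test.** Bonferroni would require 0.05/m: 0.0005 for 100 features and 0.00005 for 1,000. It holds the chance of any false positive at about 4.9% under independence. The Benjamini-Hochberg procedure is less strict: the i-th smallest p value is compared with 0.05 × i/m, so the bar equals Bonferroni's only for the smallest p value.

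**The case against.** The strongest reply is that the threshold sentence is a conventional statement of alpha. It sits among t tests, chi-squared tests and regression and never names methylation, miRNA or microbiota. They are reached only through the word *each*. The protocol describes no assay and no molecular analysis method, so these details may sit in a plan that is not shown. This limits how much can be said about size, and it is why the figures above are conditional. It does not remove the rule. The wording admits no exception, and the final section repeats it without one.

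A reader might infer that false biomarker claims are certain. The protocol does not support that. It gives no feature count, and near-certainty needs roughly 100 null features. Nor is a nominally significant feature already a biomarker claim: the summary speaks of what the analysis could provide, and the secondary aims are mostly worded as investigations.

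Three further extensions are tempting and do not hold:

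- **Genetic risk.** The aim of defining genetic risk of gestational diabetes is a risk-association question, not a comparison of diets. The argument about a diet with no effect does not apply to it.
- **Regression only for significant outcomes.** The final section fits logistic models "for the primary and secondary outcomes that were significantly different in the univariate analysis". This is selective modelling. It creates no additional false positives, and the section's remark about few events points to binary clinical outcomes rather than molecular features. The April 2017 addendum also provides a crude relative risk for each outcome of interest, so estimation is not confined to significant results.
- **The 0.15 screen.** The rule "Variables showing a p value under 0.15 in the univariate analysis will be selected for the multivariate analyses" governs entry to multivariate models and is not a claim of significance.

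**Conclusion.** The point holds in conditional form. The protocol states an unadjusted 5% rule for each test, and its wording covers the methylation, miRNA and microbiome outcomes in women and offspring. If features are tested singly under that rule, about 5 in every 100 true nulls will be declared significant. The chance of at least one false positive runs from 23% at 5 features to over 99% at 100, assuming independent true nulls. The actual size cannot be fixed from the protocol, because the number of features is not given.

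The single primary outcome keeps its 5% level, and its sample size stands. The change should be made before molecular results are interpreted, because the secondary mechanistic findings are the ones exposed. It is not a reason to doubt the primary analysis.

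**What to change.** Replace the blanket rule with one paragraph that does the following:

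- It limits the p<0.05 decision rule to the primary outcome, gestational diabetes at 24–28 weeks.
- It defines the molecular families (methylation, miRNA and microbiome, each in women and in offspring), states the number of features in each, and declares findings within a family by a prespecified false discovery rate, such as Benjamini-Hochberg at 5%.
- It reports the remaining secondary outcomes as estimates with 95% confidence intervals, labelled exploratory.

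The particular procedure and the grouping are choices, and another prespecified method would serve. Six families at 5% each still leave up to 1 − 0.95^6 = 26% for at least one false declaration somewhere if every null is true and the families are independent. The molecular results should therefore also be called exploratory unless the families are combined or adjusted jointly.

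The cost is a short amendment and a standard software option, with no extra women, samples or visits. Fewer secondary findings will be nominally significant. If a separate analysis plan already contains such control, the protocol's sentence should be brought into line with it.

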### **ETHIC, DEONTOLOGICAL AND REGULATORY CONSIDERATIONS**

The Investigator will ensure that this study is conducted in accordance with the principles of the Declaration of Helsinki, ICH Guidelines for Good Clinical Practice and in full conformity with relevant regulations. The protocol, informed consent form, participant information sheet and any applicable documents will be submitted to an appropriate Ethics Committee (EC) and Regulatory Authority for written approval. The trial staff will ensure that the participants' anonymity is maintained. The participants will be identified only by a participant ID number on the CRF and any electronic database. All documents will be stored securely and only accessible by trial staff and authorized personnel. The study will comply with the Data Protection Legislation which requires data to be anonymized as soon as it is mandatory to do so.

# ADENDUM, November 30, 2014

- IG will be provided 10 L of EVOO and 2 kgs of pistachios at 12-14 GWs (Visit 1) for free, to ensure compliance to the intervention of at least 12 weeks before attending GDM screening.
- Pistachios are chosen as nuts for IG, because their consumption can decrease appetite and involve glucose- and insulin-lowering effects. Consequently, serum  $\gamma$ -tocopherol, a biomarker of pistachio intake, will be assessed.
- Adherence biomarkers will be measured at baseline and at 24-28 GW in 10% of participants randomly selected from the IG and CG.
- The 14-point Mediterranean Diet Adherence Screener (MEDAS) will be also used to obtain the MEDAS-derived PREDIMED score (**Figure 3**).
- The study will be single-blinded. The staff involved in the trial (doctors, midwives, evaluator...) might know of the pregnant women's participation in the study, but whether they belong to the CG or IG will remain unknown, excepting to the dieticians. Between 12-14 and 24-28 GWs there will be no visits programmed by the staff of the trial.

Figure 3- MEDAS questionnaire.

| Questions                                                                                                                              | Criteria for 1 point              |
|----------------------------------------------------------------------------------------------------------------------------------------|-----------------------------------|
| 1. Do you use olive oil as main culinary fat?                                                                                          | Sí                                |
| 2. How much olive oil do you consume in a given day (including oil used for frying, salads, out-of-house meals, etc.)?                 | ≥4 tbsp                           |
| 3. How many vegetable servings do you consume per day? (1 serving : 200 g [consider side dishes as half a serving])                    | ≥2 (≥1 portion raw or as a salad) |
| 4. How many fruit units (including natural fruit juices) do you consume per day?                                                       | ≥3                                |
| 5. How many servings of red meat, hamburger, or meat products (ham, sausage, etc.) do you consume per day? (1 serving: 100–150 g)      | <1                                |
| 6. How many servings of butter, margarine, or cream do you consume per day? (1 serving: 12 g)                                          | <1                                |
| 7. How many sweet or carbonated beverages do you drink per day?                                                                        | <1                                |
| 8. How much wine do you drink per week?                                                                                                | ≥7 glasses                        |
| 9. How many servings of legumes do you consume per week? (1 serving : 150 g)                                                           | ≥3                                |
| 10. How many servings of fish or shellfish do you consume per week? (1 serving 100–150 g of fish or 4–5 units or 200 g of shellfish)   | ≥3                                |
| 11. How many times per week do you consume commercial sweets or pastries (not homemade), such as cakes, cookies, biscuits, or custard? | <3                                |
| 12. How many servings of nuts (including peanuts) do you consume per week? (1 serving 30 g)                                            | ≥3                                |
| 13. Do you preferentially consume chicken, turkey, or rabbit meat instead of veal, pork, hamburger, or sausage?                        | Sí                                |

|                                                                                                                                                                                            |    |
|--------------------------------------------------------------------------------------------------------------------------------------------------------------------------------------------|----|
| 14. How many times per week do you consume vegetables, pasta, rice, or other dishes seasoned with sofrito (sauce made with tomato and onion, leek, or garlic and simmered with olive oil)? | ≥2 |
|--------------------------------------------------------------------------------------------------------------------------------------------------------------------------------------------|----|

*Natural fruit juice and alcohol consumption will not be accounted for. Adapted from Martínez-González MA et al.*

*PLoS ONE. 2012; 7(8): e43134.*

## Final statistical analysis

### Sample size

For sample size calculation the primary end-point was the incidence of GDM between 24-28 GWs. We estimated that 315 women per group would be required to provide statistical power of 80% (2-tailed  $\alpha = 0.05$ ) to detect a relative risk reduction of at least 30% after intervention assuming an incidence of 35% GDM in the control group. Previously, this intervention has shown a decrease of the median of fasting blood glucose (FBG) -0.38 mmol/L after 3 months, representing a potential reduction of GDM rate higher than 30%. Taking into account loss to follow-up, we included 1000 successive women that attended their first ultrasound visit at the Obstetrics department between 12-14 GW, to guarantee a minimum duration of 12-weeks of intervention.

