## **OBJECTIVES:**

### **Primary outcome:**

- To define the prevention of GDM (evaluated at 24-28 GWs with HAPO criteria) after the lifestyle intervention based on MedDiet and physical activity/exercise, as compared to standard treatment, in women with normal FPG (<92mg/dL) at the 1st gestational visit (8-12 GWs).

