### ***Follow-up***

Women will be enrolled at 8-12 GWs (visit 0) and will follow-up at GWs 12-14 (visit 1), 24-28 (visit 2), 34-36 (visit 3) and delivery (visit 4), as well as at 12 weeks (visit 5) and 1 year post delivery (visit 6).

Baseline assessments (Visit 0): Women will be evaluated after the signature of the informed consent form. A complete medical history and physical exam will be performed. Subsequent assessments (Visits 1-6): Women will be followed up by means of clinic visits by the study staff. Six clinic visits will be performed, including: assessment of endpoints/outcome measures, assessments of safety including general (e.g. physical examination), specific safety assessments (e.g. blood chemistries including general biochemistry, hematology and urine analyses) and adverse event collection, assessment of compliance with the study and recording of concomitant medications. Blood and stool samples will be taken at this time. At visit 5 and 6, cord blood and placenta will be taken.

All biological samples will be extracted in one point and will be supervised by a scientist staff that will ensure fit for-purpose operations (high-throughput, high-quality). Design and testing of the sample-handling protocol will consider key factors that could affect the stability of biological samples, including anti-coagulants, stabilizing agents, temperature, and elapsed time from collection to initial processing and endogenous

degrading properties (enzymes). Sample fractions will be stored in two separated ultra-low temperature freezers to ensure long-term stability and integrity.

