## TEAM.

The Department of Endocrinology and Metabolic Diseases of the Hospital Clínico San Carlos is a leading research group in the field of prevention and epidemiology of diabetes in Spain. Its personnel have been involved in various landmark projects on public health aspects of diabetes, and cardiovascular diseases, in Spain and in many other countries. In the last years, the group has developed an interest in GDM, establishing a close collaboration with the Department of Gynaecology and Obstetrics of the Hospital Clínico San Carlos.

In this project, each gynaecologist/obstetric investigator will be responsible for recruiting patients, asking for and obtaining written informed consent, evaluating inclusion and exclusion criteria and notifying the patient inclusion to the coordinator. They will also be responsible of random group assignment, program patient visits according to the study protocol and data collection. For this task, age, sex, education level (no studies, elementary, secondary, technical school or university graduate), marital status (single, divorced, married or living together as a couple or widowed) smoking habits (current vs. non-smoker), leisure-time sports (days per week and hours per day), family history of diabetes or metabolic syndrome, personal obstetric history and history of hypertension, dyslipidemia or coronary heart disease will be recorded. Weight, height and waist and hip circumferences will be directly measured by the research physician using standardized methods. Since women who developed GDM will need intensive blood sugar control to prevent maternal and fetal complications and treatment with dietary or medication therapy based on their individual needs, endocrinologists will follow them. They will be simultaneously followed by their obstetricians for appropriate monitoring of the pregnancy. A dietician will carry out lifestyle interventions for all women. They will be developed during a 1-h session (Visit 1) for each woman individually and will be reinforced at each follow-up visit. We have developed a questionnaire to evaluate adherence to recommended lifestyle changes (*Table 1*). A score of +1, 0 or -1 has been assigned to each of the 18 items on the questionnaire, with a value of +1 indicating that the beneficial recommendation is regularly performed, -1 indicating that the beneficial recommendation has not been adopted or that patients are persisting with an unhealthy habit, and 0 indicating

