**- Intervention group (IG).** Women with free allotments of EVOO (1 litre/week) and pistachios (150 g/week), and the training program. Dieticians gave personalized dietary advice to participants with instructions directed to use of EVOO for cooking and dressing, increased consumption of fruit, vegetables, legumes, and fish and avoidance of red or processed meat, butter, cream, fast food, sweets, pastries, and sugar-sweetened beverages. This intervention diet is comprised of an intake of approximately 35-40% of total fat (predominantly unsaturated fatty acids) and 40-45% of low glycemic index carbohydrates, maintaining a protein intake of 20%, similar to the control diet. The dietician was responsible of giving nutritional advice to women at Visits 1 (12-14GW), 2 (24-28 GW) and 3 (36-38 GW). This was done in order to benefit from the already-programmed visits to the clinical analysis.

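### The visit windows secure only about 10 weeks of intervention before the GDM test, not the 12-week minimum the protocol states

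*Protocol*

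**What the plan says.** Two places in the Protocol give a 12-week minimum.

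- Final statistical analysis, Sample size: inclusion is described as women "that attended their first ultrasound visit at the Obstetrics department between 12-14 GW, to guarantee a minimum duration of 12-weeks of intervention". The same paragraph names GDM at 24-28 GW as the primary endpoint.
- Addendum of November 30, 2014: "IG will be provided 10 L of EVOO and 2 kgs of pistachios at 12-14 GWs (Visit 1) for free", and the stated reason is "to ensure compliance to the intervention of at least 12 weeks before attending GDM screening". This is the only place that says outright that the 12 weeks fall before the GDM test.

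The schedule is set elsewhere.

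- Follow-up: women "will follow-up at GWs 12-14 (visit 1), 24-28 (visit 2").
- Team, on the lifestyle sessions: "They will be developed during a 1-h session (Visit 1) for each woman individually".
- Addendum of May 4, 2017, intervention group: "The dietician was responsible of giving nutritional advice to women at Visits 1 (12-14GW), 2 (24-28 GW").
- Primary outcome: "To define the prevention of GDM (evaluated at 24-28 GWs with HAPO criteria").
- Addendum of November 30, 2014: "Between 12-14 and 24-28 GWs there will be no visits programmed by the staff of the trial".

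**The concern.** Both statements describe a floor that every woman meets, not an average or a target. A floor on exposure follows from visit windows only if the latest permitted start and the earliest permitted test are at least that far apart. Here they are not, and nothing else in the text closes the gap.

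The figure is not decorative. The Sample size text supports its 30% relative reduction by a fall in fasting glucose seen after 3 months of the diet in an earlier trial, and a 12-week minimum is roughly that period. A reader who relies on the floor would take it that every woman had about the exposure behind the effect assumption by the time of her test. The schedule does not secure that. What is at stake is how exposure before the primary endpoint is described, not the validity of the comparison.

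**Working it through.** **Inputs**

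- Start of intervention: Visit 1, 12-14 GW (Team; addenda of November 30, 2014 and May 4, 2017).
- GDM test: 24-28 GW (Primary outcome; Follow-up; Sample size).
- Stated minimum: 12 weeks (addendum of November 30, 2014; Sample size).

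**Reproducing the stated 12 weeks**

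Earliest test minus earliest start: 24 - 12 = 12 weeks. The figure appears when both windows are taken at their early ends. That is the shortest interval for a woman who enters at 12 GW, not for all women.

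**Interval that the windows permit**

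- Minimum = earliest test - latest start = 24 - 14 = 10 weeks.
- Maximum = latest test - earliest start = 28 - 12 = 16 weeks.

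| Entry (Visit 1) | Shortest interval | Longest interval | Largest shortfall against 12 | Earliest test that meets 12 weeks |
|---|---|---|---|---|
| 12 GW | 24 - 12 = 12 | 28 - 12 = 16 | 0 | 12 + 12 = 24 GW |
| 13 GW | 24 - 13 = 11 | 28 - 13 = 15 | 1 | 13 + 12 = 25 GW |
| 14 GW | 24 - 14 = 10 | 28 - 14 = 14 | 2 | 14 + 12 = 26 GW |

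**Sensitivity to how a gestational week is counted**

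The table treats the window ends as exact weeks. If 14 GW includes 14 weeks and 6 days, the minimum is 24 weeks 0 days less 14 weeks 6 days, which is 9 weeks 1 day. The protocol does not say which convention it uses.

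**Alternative start**

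The project summary and the study hypothesis place the start after the 8-12 GW visit. Counted from that visit itself, the interval is 24 - 12 = 12 to 28 - 8 = 20 weeks, and the floor would hold.

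**Is the sample size affected?**

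The inputs are 35% and 0.35 × 0.70 = 24.5%, two-sided 5%, 80% power. The standard two-proportion formula gives 297 per group without continuity correction and 316 with it, so the stated 315 is reproduced to rounding with the correction. Duration of intervention does not enter the formula.

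**The case against.** The strongest reply is that floor and windows do not contradict each other. Every entry week has a test date inside 24-28 GW that meets 12 weeks, so the two can be read together: 24-28 GW as the window and 12 weeks as an added condition. On that reading only a booking rule is missing. Part of this stands, because the table shows the floor to be attainable. But neither place states 12 weeks as a condition on the test date. The Sample size text presents it as a consequence of entry at 12-14 GW, and the November 2014 addendum as a consequence of giving supplies at that visit. Neither step secures it.

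A second reply is that the Sample size sentence does not itself say that the 12 weeks precede the test, and the intervention continues through pregnancy. That is correct. A reader might infer that both places say so outright, but only the addendum does. For the Sample size text the reading rests on context, namely the 24-28 GW endpoint in the same paragraph. The point holds on the addendum alone.

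A third reply is the earlier start in the project summary and hypothesis. It does not rescue the claim. The Sample size text ties its minimum to 12-14 GW, the session and the supplies are fixed at Visit 1, and a start after the 8-12 GW visit is compatible with Visit 1.

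A fourth reply is that the tests are probably done. The later sections are in the past tense, and the addendum of April 1, 2017 reports convergence problems met in model fitting. This stands, and it makes the correction of the text more likely to matter than the booking rule.

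**Conclusion.** The 12-week minimum is not secured by the schedule as written. The windows alone secure 10 weeks, or just over 9 under the completed-week reading, so the shortfall is at most 2 weeks, or just under 3. This rests on Visit 1 being the start of the intervention and on the absence of any rule linking a woman's test date to her own Visit 1.

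The point is minor. Four stronger conclusions are tempting, and the documents support none of them.

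- *That some women had less than 12 weeks.* The windows permit it, but no dates are given. The number of such women may be zero, and any share would rest on an assumed spread of visits.
- *That the true duration was 10 to 16 weeks.* That is the permitted range, not an observed one, and its ends move with the week-counting convention.
- *That the comparison is biased or the trial too small.* The windows are the same in both arms. The 315 per group is reproduced without using duration, and the documents give no relation between weeks of diet and effect from which to recompute it.
- *That the supplies ran out early.* At the weekly allotments in the Intervention section, 10 L of oil covers 10 / 1 = 10 weeks, but the pistachios handed over with it cover 2000 / 150 = 13.3 weeks. The nominal amounts point in different directions and show no shortfall in exposure.

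**What to change.** **For any woman not yet tested, in both arms:** book the GDM test within 24-28 GW and at least 12 weeks after her own Visit 1. That means no earlier than 24, 25 or 26 GW for entry at 12, 13 or 14 GW. Counting the 12 weeks as 12 × 7 = 84 days from the Visit 1 date avoids the week-counting question. Even entry at 14 weeks 6 days then gives a test at 26 weeks 6 days, inside the window.

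**For women already tested:** delete the 12-week minimum from the Sample size text and the matching statement in the November 2014 addendum, unless the recorded dates confirm it for every woman. Do not put a range derived from the windows in its place. Report the observed weeks from Visit 1 to GDM test by arm.

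**Cost:** a wording change in two places, one derived variable from dates of scheduled visits, and a booking rule only if anyone remains to be tested. The sample size and the analysis models stay as they are.
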